### Outcomes

The primary endpoint was the change in average daytime ambulatory SBP from baseline to the end of treatment (3 months). Both assessments of average daytime ambulatory SBP were calculated using ABPM recordings between 7 a.m. and 11 p.m. on the day of the assessment. Secondary endpoints, detailed in Supplementary Table 5, included changes in 24-h ambulatory and office SBP and DBP, ambulatory HR, BP variability, HR variability, quality of life, and sleep quality from baseline to end of treatment.

### Exploratory endpoints and sub-studies

The trial also collected data throughout the study (Supplementary Table 4) to assess various exploratory endpoints (see Supplementary Table 6 for details.) These included feasibility endpoints to assess the safety and acceptability of the device for patients, echocardiographic markers, and central BP measurements at baseline and end of treatment to explore the potential broader cardiovascular effects of tAN. Plasma and serum samples were also stored at −80°C from blood collected at baseline, week 4, and week 12 visits for all patients for subsequent analysis of proteomics, inflammatory markers, and metabolomics.

For a subgroup of consented patients (*n* = 22), we completed a sub-study of several detailed physiological tests, commonly known as Autonomic Target-Organs Neurophysiological tests (ATONT), at baseline and week 12 (end of treatment), to explore the potential mechanism underlying the effects of tAN. ATONT takes approximately 90 min to complete and includes continuous measurements of heart rate, beat-to-beat BP, tissue oxygenation, respiratory rate, and ECG monitoring. Participants also completed simple physiological manoeuvres: standing from lying position, hand-grip, sit up, Valsalva manoeuvre, and carotid massage.

### Sample size

The trial was powered for the primary endpoint (change in daytime ambulatory SBP between baseline and the end of the treatment at 12 weeks) in the active treatment arm. This was done using a paired *t*-test approach.

Using a conservative assumption of a mean change in SBP of 5.5 mmHg with a standard deviation of 11 mmHg, based on the existing data for hypertensive patients, 34 participants were required to give 80% power to detect such a change at the two-sided alpha level of 0.05. After inflation for a potential 10% drop-out and a further 10% non-compliance, we required 42 subjects in the intervention (tAN) arm.

The study also recruited participants to be randomised to the sham-tAN arm to compare changes in SBP in those undergoing treatment to consider potential Hawthorne and placebo effects. In order to collect more data regarding safety in the active treatment group, the trial recruited double the number of subjects for the active treatment than for the sham treatment—a randomisation ratio of 2:1. Therefore, the sample size for the sham-tAN treatment was 21, with a total sample size across both arms of 63 subjects.

The sample size of 63 subjects (42 tAN, 21 sham), using a 2:1 randomisation ratio, provided 80% power to detect a between-arm difference of 8.4 mmHg in daytime SBP assuming no attrition, or 9.3 mmHg assuming a 20% attrition (10% dropout plus 10% non-compliance).

### Statistical methods

Baseline demographic and physiological characteristics will be presented separately by trial group. The main analyses of the primary and secondary endpoints will be conducted on an intention-to-treat population (all randomised participants with available data irrespective of their compliance with the device) and on a per-protocol population (all participants with treatment compliance on 80% or more days during the trial). Any participants who required a change in antihypertensive medication during the treatment period for safety/ethical reasons or otherwise will be included in the intention-to-treat analyses but not in the per-protocol analyses.

The primary endpoint, change in daytime ambulatory SBP, will be calculated for each participant by subtracting the end-of-treatment measurement (at 3 months) from the baseline measurement. The mean change in daytime SBP within each group will be presented with 95% confidence intervals (CIs) within the active treatment arm. The crude difference in the mean change in daytime SBP between treatment arms will be calculated with a 95% CI, and a two-sample *t*-test with equal variances will be used to test the null hypothesis of no difference in the change in SBP between groups.

Adjusted analyses will be conducted using linear regression, comparing change in SBP between treatment groups while adjusting for baseline daytime ABPM SBP (ANCOVA), age, sex, and BMI. The estimated adjusted difference in change in SBP will be presented, along with 95% CIs and *p*-values. The primary endpoint will also be analysed according to subgroups defined by (i) BMI at baseline (<30 kg/m^2^ vs. ≥30 kg/m^2^), (ii) diabetes status at baseline, (iii) age at baseline (<65 years vs. ≥65 years), and (iv) mean ABPM daytime SBP at baseline (<160 mmHg vs. ≥160 mmHg); for each of these four risk factors, a test for interaction will be conducted between groups. Moreover, data from the urinary antihypertensive drug screening samples collected at visits 2, 4, and 5, providing objective longitudinal data on antihypertensive medication adherence for each participant from the point of randomisation to end of treatment, will be used to adjust the analysis of the primary outcome for partial or non-compliance to medications.

All secondary endpoints that are continuous will be analysed in the same way as for the primary endpoint. Binary endpoints will be displayed as the whole number of subjects who meet that endpoint at the end of the study alongside the total number of subjects in that group. A percentage of subjects meeting that endpoint for each group will also be recorded. For binary endpoints, the crude and adjusted odds ratios (ORs) will be estimated.

All feasibility endpoints for this phase 2a study will be presented descriptively or analysed qualitatively.

We will also summarise AEs using counts and percentages and present these overall for the study and by treatment arm. The number of subjects with AEs of mild/moderate/severe intensity will be shown overall and by treatment arm using the maximum severity experienced by each participant. The total number of AEs for each treatment, allowing multiple events per participant, will also be presented.

Serious AEs (SAEs; both non-fatal and fatal) will be listed separately along with details of the treatment and whether the event is unexpected or thought to be related to the treatment.

No interim analyses of any endpoint were planned. The full statistical analysis plan is provided in Supplementary Material 3, and the full clinical investigational plan is provided in Supplementary Material 4.

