Participants self-administered the treatment using the device for 14 consecutive days, 30 min each evening. During this period, participants received two phone calls as reminders to apply treatment daily for the duration of the initial course of treatment and complete device procedure and device logbook entries. Concomitant medication and adverse events (AEs) were simultaneously reviewed.

After 14 days, visit 3 was conducted where medications, logbooks, and AEs were reviewed. The participants also underwent office BP measurement, vital sign assessment, and 6 MWT and completed the cognitive assessment, adherence, and QoL questionnaires. Participants were then asked to self-administer therapy once a week for a further 10 weeks.

Visit 4 took place on Day 28. At this visit, vital signs, 24-h ABPM, office BP, 24-h Holter ECG, and 6 MWT were assessed, and a review of concomitant medication(s), use of the device, logbook, and AEs was completed. Participants had their blood and urine samples collected for safety and medication adherence assessments and also completed cognitive assessment and questionnaires on device usability, QoL, insomnia, and blinding. Email/text reminders to complete the device procedure and logbook entry were sent at Day 42. A phone call was conducted at Day 56 reminding participants to continue using the device and completing logbook entries, while concomitant medication(s) and AEs were reviewed. Another email/text reminder was sent on Day 70.

The end-of-treatment visit (visit 5) took place at the end of week 12 (Day 84). Participants completed the following assessments: vital signs, weight and BMI, 24-h ABPM, office BP, central BP, 24-h Holter ECG, 6 MWT, echocardiogram, and safety blood and urine samples. Concomitant medication(s), device logbooks, and AEs were reviewed, and the device was returned. Participants then completed all trial questionnaires and the final cognitive assessment.

After the trial, follow-up was conducted at week 16 (Day 112) with a phone call to review concomitant medication(s), AEs, and the QoL remotely.

In addition, an extra visit/clinical assessment was offered as per each participant's clinical requirement, particularly for those with either high (SBP > 180 mmHg) or low (SBP < 100 mmHg) BP, symptomatic postural hypotension, or other clinical concerns.

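### The main 'intention-to-treat' analysis is a complete-case analysis at Day 84, and no stated primary model uses the Day 28 ABPM

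*Protocol article*

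**What the plan says.** The Statistical methods section states: "The main analyses of the primary and secondary endpoints will be conducted on an intention-to-treat population", alongside a per-protocol set. It defines the intention-to-treat set as "all randomised participants with available data irrespective of their compliance with the device". The primary endpoint "will be calculated for each participant by subtracting the end-of-treatment measurement (at 3 months) from the baseline measurement", so both ABPMs are needed.

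Two between-arm analyses follow. In the crude one, "a two-sample *t*-test with equal variances will be used to test the null hypothesis of no difference in the change in SBP between groups". The adjusted one is described as "Adjusted analyses will be conducted using linear regression, comparing change in SBP between treatment groups while adjusting for baseline daytime ABPM SBP (ANCOVA), age, sex," with BMI as the last covariate. Continuous secondary endpoints are handled the same way.

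The Procedure section and Table 2 schedule another ABPM between baseline and Day 84. "Visit 4 took place on Day 28", and "At this visit, vital signs, 24-h ABPM, office BP, 24-h Holter ECG, and 6 MWT were assessed". The Sample size section expects losses: the active arm was set at 42 "After inflation for a potential 10% drop-out" and a further 10% for non-compliance.

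**The concern.** Restricting the set to available data, defining the endpoint as a two-point change and using single-time-point tests together exclude every participant who lacks the Day 84 recording. The ANCOVA is unbiased only if, within arm, loss is unrelated to outcome given baseline SBP, age, sex and BMI. The t-test needs this without the covariates.

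Early response is a plausible reason for leaving, and Day 28 measures early response with the same instrument as the endpoint. The stated models cannot use that information for those who leave after visit 4. With 42 and 21 participants, a few such losses can move an arm mean. The within-arm change in the active arm, for which the trial is powered, has no comparator to absorb a shift.

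**Working it through.** **The plan's own figures.** Inputs from the Sample size section: change 5.5 mmHg, SD 11, two-sided alpha 0.05, power 80%, allocation 42:21.

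- Paired t-test, effect 5.5/11 = 0.5: n = 33.4, so 34. Inflation: 34/0.9/0.9 = 41.98, so 42.
- Two-sample t-test: detectable difference 8.37 mmHg at 42/21 and 9.34 at 34/17, against the stated 8.4 and 9.3.

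All four figures reproduce. The sample size is not in question.

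**Expected loss.** 0.10 × 63 = 6.3, about 4 active and 2 sham. Power for 8.4 mmHg falls from 80.3% (42/21) to 76.1% (38/19).

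**Shift of an arm mean.** If k of n are lost and their change would have been 10 mmHg less favourable than in completers (an assumption), the mean shifts by 10 × k/n.

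| Lost | Shift |
|---|---|
| 4 of 42 active | 10 × 4/42 = 0.95 mmHg |
| 2 of 21 sham | 10 × 2/21 = 0.95 mmHg |
| 4 of 21 sham | 10 × 4/21 = 1.90 mmHg |

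With 4 active and 2 sham lost, the shifts cancel between arms: 0.95 − 0.95 = 0. The active-arm change is still overstated by 0.95 mmHg, which is 0.95/5.5 = 17% of the planned change. With 4 lost in each arm, the between-arm difference is off by 1.90 − 0.95 = 0.95 mmHg.

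**Simulation.** Assumptions: change SD 11 at both visits, true difference −8.4 (negative means a greater fall on active), Day 28 seen in all, no baseline covariates, 2,000 runs per case. The participants lost are those with the worst Day 28 change plus noise of SD 5. The documents give no Day 28–Day 84 correlation, so 0.3 to 0.7 is used.

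| Loss sham / active | Complete-case mean at r = 0.3, 0.5, 0.7 | Bias (mmHg) | Mean using Day 28 |
|---|---|---|---|
| 20% / 10% | −7.99, −7.75, −7.47 | 0.41, 0.65, 0.93 towards no effect | −8.42, −8.42, −8.44 |
| 10% / 20% | −8.90, −9.04, −9.50 | 0.50, 0.64, 1.10 away from no effect | −8.45, −8.28, −8.42 |

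With equal loss (10% or 20% in both arms) selected the same way, complete cases average −8.42 to −8.51, close to the truth. The Monte Carlo error is about 3.1/√2000 = 0.07.

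**Precision.** With a fraction m = 0.10 missing at random, the variance of an arm mean relative to no loss is 1/(1 − m) = 1.111 for complete cases and (1 − m r²)/(1 − m) when Day 28 is used:

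- r = 0.5: 0.975/0.9 = 1.083; standard-error ratio √0.975 = 0.987, or 1.3% lower.
- r = 0.7: 0.951/0.9 = 1.057; ratio √0.951 = 0.975, or 2.5% lower.

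In the simulated unequal-loss cases that depended on Day 28, the estimate using Day 28 was no more precise (20%/10% loss: empirical standard error 3.29 against 3.17 at r = 0.3, and 3.16 against 3.15 at r = 0.7). The argument for the model is therefore bias, not precision.

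**The case against.** The strongest reply has four parts.

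1. **Scope.** The full statistical analysis plan is a supplement that is not shown, and it may contain imputation, repeated-measures or shift analyses. A reader might infer that the trial has no strategy for missing data. The article does not support that; the point is confined to the set, label and models it prints.
2. **Routes already closed.** Participants who use the device poorly, or whose antihypertensive drugs are changed, stay in the intention-to-treat analysis, and extra visits are offered for very high pressure. This stands. The problem is limited to people with no Day 84 ABPM at all.
3. **Size.** A reader might set a 1.9 mmHg error in the sham mean against the detectable 8.4 mmHg. That compares one arm's shift with a between-arm difference. It also needs 4/21 = 19% sham loss, about twice the planned drop-out. At the planned rate in both arms, the between-arm shift is zero. The simulated 0.4 to 1.1 mmHg needs unequal loss and is small beside a standard error of 11 × √(1/42 + 1/21) = 2.94 mmHg.
4. **Remedy.** A mixed model assumes missing at random, and Day 28 helps only those who attended visit 4. Both limits stand.

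The definition is also printed beside the term, so an attentive reader can see what the set is. None of this changes the fact that the stated main analysis drops participants whose Day 28 value could inform the Day 84 estimate under a weaker assumption.

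**Conclusion.** The point holds in moderate form. As printed, the main analysis is complete case under an intention-to-treat label, and no stated primary model uses the Day 28 ABPM.

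The between-arm bias matters when loss is related to early response and differs by arm. It is about 0.4 to 1.1 mmHg at 20% against 10% loss, in either direction, under the simulation's assumptions. With equal loss it largely cancels, and what remains is a possible shift in the active-arm change, about 0.95 mmHg for 4 of 42 lost under the assumed 10 mmHg gap. If loss is random there is no bias, and the gain is 1 to 2.5% in standard error at assumed correlations of 0.5 to 0.7.

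The documents give neither the correlation nor the pattern of drop-out, so these sizes are illustrations. This is a cheap improvement worth making. It does not invalidate the trial.

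**What to change.** Before unblinding, make the adjusted primary analysis a repeated-measures mixed model:

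- **Outcome:** daytime ABPM SBP at Day 28 and Day 84 (equivalently its change, since baseline is in the model).
- **Terms:** arm-by-visit, baseline-by-visit, age, sex and BMI, with a small-sample degrees-of-freedom correction.
- **Set:** every randomised participant with any post-baseline ABPM.
- **Estimates:** the treatment effect and the active-arm change, both read at Day 84. Because device use moves from daily to weekly after Day 14, Day 28 should inform Day 84 through the model and not be carried forward.

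Keep the t-test and ANCOVA, labelled *complete case*. Report loss by arm and whether it came before or after visit 4. Confirm that the statistical analysis plan includes a missing-not-at-random sensitivity analysis, because the model assumes missing at random and does not recover those lost before visit 4.

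The article anticipates results in early 2026. If the data are already unblinded, report the model as a labelled supplementary analysis.

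The cost is wording and modest programming, with no new data. The downside is a slightly more complex model.

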### Procedure

Trial participants were required to attend five visits spanning 12 weeks/84 days: visit 1 for the screening; visit 2 for baseline and randomisation at Day 0; visit 3 at Day 14; visit 4 at Day 28; and visit 5 for the end of treatment at Day 84 (see Figure 2 for Flowchart). Participants also received several telephone calls: one between days 1 and 3, one on Day 7, one at Day 56, and one at Day 112 (post-trial follow-up). Participants received text and/or email reminders at Day 42 and Day 70. The expected total duration of participation was 16 weeks. No changes in antihypertensive medications were permitted during the trial (between randomisation on Day 0/visit 2 and end of treatment on Day 84/visit 5). Table 2 summarises the assessments and data collected at each visit with a full detailed schedule provided in Supplementary Table 4.

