## Discussion

The SCRATCH-HTN trial is a double-blind, sham-controlled study evaluating the safety and acceptability of tAN using the AffeX-CT device and a novel stimulation algorithm for the first time in human subjects. The trial employs an improved protocol involving bilateral tragus stimulation. In addition to assessing safety, the study investigates the potential efficacy of tAN in reducing BP in patients with uncontrolled hypertension despite ongoing treatment. The findings are expected to pave the way for further evaluation of this innovative technology and establish it as a viable therapeutic option. Through the number of secondary and exploratory endpoints and the sub-study, the SCRATCH-HTN trial is designed to be hypothesis-generating. By examining the effects of tAN on sleep quality, exercise tolerance, heart rate variability, central BP, cardiac structure, and autonomic function, the study aims to provide mechanistic insights and data on related potential therapeutic benefits that may inform future studies. If effective, or if tAN demonstrates efficacy within the constraints of statistical power considerations, tAN could represent a transformative approach to hypertension management, fostering further research into this device and its applications in the field.

The study was carefully designed to mitigate known risks associated with device-based and non-pharmacological interventions in hypertension trials. The trial participants were required to have uncontrolled BP despite receiving medication, who were asked to avoid any changes in their medication. Although there is an increased risk of cardiovascular sequelae from uncontrolled hypertension, the trial duration was just 12 weeks, a shorter period than that which patients invariably wait between community and secondary care visits following dose escalation. Those patients at higher risk with recent complications of hypertension such as stroke, myocardial infarction, or decompensated heart failure that require strict control of BP were excluded from the trial at screening. Moreover, we carefully monitored the patients during the trial period and if their BPs were at levels that could potentially damage target organs acutely, for example, mean average office SBP > 180 mmHg or DBP > 120 mmHg, we allowed the introduction of another medication or escalation of existing antihypertensive treatment as per the current guidelines and their physician’s advice.

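### Intention-to-treat and per-protocol analyses are both called main with no ranking, and per-protocol removes participants after randomisation for medication changes that can be triggered by high on-trial blood pressure

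*Protocol article*

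**What the plan says.** All of this is in the Protocol article.

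- **Statistical methods, populations.** "The main analyses of the primary and secondary endpoints will be conducted on an intention-to-treat population", defined as "all randomised participants with available data irrespective of their compliance with the device". The same sentence adds a per-protocol population, "all participants with treatment compliance on 80% or more days during the trial". Neither is placed first.
- **Statistical methods, medication changes.** A participant whose blood-pressure drugs are altered between randomisation and Day 84 "will be included in the intention-to-treat analyses but not in the per-protocol analyses". The rule covers any change for any reason, not only escalation.
- **Statistical methods, endpoint and tests.** The change is baseline minus the 3-month daytime systolic BP (SBP), with no separate rule for a 3-month value taken after a medication change. A crude two-sample t-test is planned. So is a regression adjusted for baseline SBP, age, sex and body mass index (BMI).
- **Procedure.** "No changes in antihypertensive medications were permitted during the trial", from Day 0 to Day 84.
- **Discussion.** Where BP reached potentially damaging levels, for example mean office SBP above 180 or diastolic BP above 120 mmHg, "we allowed the introduction of another medication or escalation of existing antihypertensive treatment".

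**The concern.** Two things follow from this text.

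First, with two main populations and no order between them, the article does not fix which result decides the primary endpoint. If the two disagree, either could be presented as the main finding. The crude and adjusted tests within each population widen the choice.

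Second, the per-protocol exclusion is not neutral. Escalation can be prompted by high BP during follow-up, which is closely related to the outcome. If tAN lowers BP, fewer tAN than sham participants should reach the trigger. Per-protocol would then remove more high-BP participants from sham, while ITT would count their drug-lowered 3-month value. Neither population as described estimates the effect on unchanged medication, which is the setting the Procedure section aims for. The planned adjustment from urinary drug screens is for partial or non-compliance with medication and is not described as handling added drugs.

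**Working it through.** **1. Scale: the article's own figures.** Sample size gives 80% power for 8.4 mmHg (no attrition) or 9.3 mmHg (20% attrition). The SD of 11 mmHg is stated for the paired calculation; I assume it also applies between arms.
- 42:21: standard error = 11 × √(1/42 + 1/21) = 2.94. The two-sample noncentral t gives 8.37 mmHg.
- 34:17: standard error = 11 × √(1/34 + 1/17) = 3.27. This gives 9.34 mmHg.

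Both figures reproduce.

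**2. False-positive chance with unranked analyses.** Two independent tests would give 1 − 0.95² = 9.75%. The two populations overlap, so the true figure for one test in each is lower. Null simulation, with inputs assumed: 38:19 analysed, SD 11, per-protocol a random 80% or 88% of each arm, correlation of baseline with change 0 to −0.5, adjusted test using baseline SBP, age, sex and BMI, 12,000 trials per setting.

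| Claim allowed if p < 0.05 in | Chance under the null |
|---|---|
| one named test in one population | about 5% |
| crude test, ITT or per-protocol | 6.6–7.3% |
| crude or adjusted test, ITT only | 6.0–7.6% |
| any of the four | 8.3–10.8% |

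A random per-protocol subset isolates the multiplicity; it contains no outcome-driven exclusion.

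**3. Direction and size of the escalation effect.** With escalation proportions p(sham) and p(tAN) and drug effect R, the ITT benefit falls by (p(sham) − p(tAN)) × R. The article gives no escalation rates, so these were simulated. Assumptions: baseline daytime SBP about 148 (SD 8), sham change −3, SD of change 11, office SBP 8 mmHg above ambulatory (SD 8), R = 9 mmHg, no effect in device non-compliers. The 180 trigger is the article's example; 170 is used only to generate more escalation. Benefits are in mmHg.

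| Effect in compliers | Trigger | Non-compliers | Escalated tAN / sham | No-escalation benefit | ITT | Per-protocol |
|---|---|---|---|---|---|---|
| 0 | 180 | 0% | 4.3% / 4.3% | 0.0 | 0.0 | 0.0 |
| 5.5 | 180 | 0% | 1.9% / 4.3% | 5.5 | 5.3 | 5.1 |
| 5.5 | 170 | 0% | 7.7% / 14.1% | 5.5 | 4.9 | 4.7 |
| 8.4 | 170 | 0% | 5.3% / 14.2% | 8.4 | 7.6 | 7.3 |
| 5.5 | 180 | 20% | 2.5% / 4.4% | 4.4 | 4.2 | 5.1 |
| 5.5 | 170 | 10% | 8.4% / 14.1% | 4.95 | 4.4 | 4.7 |
| 8.4 | 180 | 20% | 1.9% / 4.3% | 6.7 | 6.5 | 7.9 |

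Hand checks on the ITT shift: (0.043 − 0.019) × 9 = 0.22; (0.142 − 0.053) × 9 = 0.80.

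With full compliance, ITT and per-protocol both fall below the no-escalation benefit. With non-compliers, ITT still falls, but per-protocol can land above (5.1 against 4.4) or below (4.7 against 4.95). Dropping non-compliers removes a dilution of up to 0.20 × 5.5 = 1.1 mmHg. If escalation were commoner on tAN, for example 10% against 5% on sham with R = 5 to 10, the ITT shift reverses to +0.25 to +0.5 mmHg.

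**The case against.** The strongest case against has four parts.

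- **Ranking belongs in the analysis plan.** The full plan is Supplementary Material 3, which is not shown, and it may rank the populations. That limits the point to the article's wording. It does not remove it, because the article positively labels both populations as main and fixes the exclusion.
- **Keeping post-change BP in ITT is legitimate.** This stands. It is a treatment-policy effect, and the fix retains it as primary. The article's hypothesis is improved BP control, without an explicit condition of unchanged medication.
- **The four-test figure overreads the text.** This partly stands. Statistical methods ties the null hypothesis to the t-test and labels the regression separately as adjusted. The 9–10% therefore applies only if crude and adjusted results are treated as interchangeable; two populations alone give about 6–7%.
- **The trial is phase 2a and described as hypothesis-generating.** This lowers the stakes, but the article still names a primary endpoint and a hypothesis test.

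A reader might go further and infer that both populations pull the tAN–sham difference the same way, so that agreement between them is false reassurance. The documents do not support that. It requires a real effect with more escalation on sham, and it concerns the escalation rule alone. The per-protocol definition also drops device non-compliers, so its net direction is not fixed. Nor should a large bias be inferred. Three escalated sham participants with a 10 mmHg drug effect would move the sham mean by 3 × 10/21 = 1.4 mmHg, but both the count and the effect are invented, and this counts no escalation on tAN.

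**Conclusion.** The point holds in a limited form. The article leaves two main populations unranked, and one of them excludes participants after randomisation for an event that can be driven by the outcome. The false-positive chance rises from 5% to about 6–7%, or about 9–10% if the crude and adjusted tests are also left open. These figures rest on the assumed overlap, correlation and analysed numbers above.

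Any understatement of the effect on unchanged medication is conditional on escalation being commoner in sham. For ITT it is about 0.2–0.8 mmHg under assumed rates, small beside the 8.4–9.3 mmHg detectable difference. For per-protocol the net direction cannot be stated in advance. The attenuation and the multiplicity are separate problems: in the simulation, a true effect of zero leaves escalation equal in both arms and shifts neither population.

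Separately, the Procedure section's ban on medication changes and the Discussion's allowance for escalation do not agree as written.

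**What to change.** Before unblinding:

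1. Name ITT as the single primary population, with one primary test. The baseline-adjusted ANCOVA already planned is preferable; its covariates correspond to the minimisation factors. Make per-protocol and the crude t-test supportive. Ranking the populations alone is not enough: crude or adjusted within ITT still gives about 6–7.6%.
2. Report antihypertensive changes by arm, with timing and direction.
3. Add one supplementary repeated-measures analysis that sets ambulatory BP after a medication change to missing and uses the Day 28 recording where it precedes the change. It will not always do so, since office BP is already taken at Day 14.
4. Reconcile the Procedure and Discussion statements on medication changes. This is a matter of consistent wording; no clinical rule is proposed here.

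The cost is revised wording and one extra analysis on data already collected. The downside is that the supplementary analysis assumes missing at random after a medication change, so it should stay supplementary.

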### Randomisation

Eligible participants were randomised in a 2:1 ratio to the tAN and sham-tAN intervention arms, respectively, using the online randomisation tool “Sealed Envelope.” This tool employed block randomisation and a dynamic minimisation approach to ensure balanced allocation between treatment groups (38). The minimisation algorithm incorporated the following baseline factors: age (<65 or ≥65 years), sex, body mass index (BMI; <30 or ≥30 kg/m^2^), and mean daytime average SBP (<160 or ≥160 mmHg).

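### The between-arm null hypothesis is tied to a crude pooled t-test on change; the ANCOVA already planned on the minimisation variables is the better deciding test

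*Protocol article*

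**What the plan says.** Under Statistical methods, the primary endpoint is a change score per participant. "The crude difference in the mean change in daytime SBP between treatment arms will be calculated with a 95% CI", and the null hypothesis is attached to that crude contrast: a two-sample t-test "with equal variances will be used to test the null hypothesis of no difference in the change in SBP between groups".

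The next paragraph adds a second between-arm analysis, a linear regression of change on arm "adjusting for baseline daytime ABPM SBP (ANCOVA), age, sex, and BMI". Its result is reported in full: "The estimated adjusted difference in change in SBP will be presented, along with 95% CIs" and p-values. Nothing in the article ranks the two.

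The Randomisation section shows that these covariates are those that drove allocation: "The minimisation algorithm incorporated the following baseline factors: age", sex, BMI and mean daytime SBP, each in two categories (SBP cut at 160 mmHg). Continuous secondary endpoints follow the primary: "All secondary endpoints that are continuous will be analysed in the same way as for the primary endpoint".

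**The concern.** The plan holds a better model than the one it uses to test its hypothesis. Four things are at stake.

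- **Design.** Allocation is balanced on four variables that the stated test ignores. If those variables are prognostic, an unadjusted test after minimisation tends to be conservative.
- **Baseline imbalance.** A change score removes a chance baseline difference completely only if the slope of follow-up on baseline SBP is 1. Minimisation splits SBP once, at 160 mmHg, within an eligibility window of 135 to below 170 mmHg, so imbalance within the two categories can remain.
- **Power.** The trial is sized on a within-arm paired test. Power between arms is short at the 5.5 mmHg used for planning, so precision available from data already collected is worth having.
- **Two p-values.** With no ranking in the article, a reader cannot tell which result counts if the two disagree.

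Separately, pooling the variance is a weaker choice at 2:1 than at 1:1, because the pooled test then no longer holds its size when the arm SDs differ.

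**Working it through.** **Inputs from the Sample size section:** SD of change 11 mmHg; planning change 5.5 mmHg; two-sided alpha 0.05; power 80%; 42 tAN and 21 sham; 10% dropout and 10% non-compliance.

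**Assumed, not in the article:** slope b of Day 84 on baseline daytime SBP; baseline SD s0.

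**1. The plan's own figures.**
- Paired t-test, 5.5 with SD 11: n = 34 gives 80.8% power (n = 33 gives 79.5%). 34 / (0.9 × 0.9) = 41.98, so 42.
- Between arms, 42:21: SE = 11 × √(1/42 + 1/21) = 2.94; detectable difference by noncentral t = 8.37 mmHg (stated 8.4).
- Between arms, 34:17: SE = 11 × √(1/34 + 1/17) = 3.27; detectable difference 9.34 mmHg (stated 9.3).
- Power of the crude test at 5.5 mmHg, 42:21: 45%.

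All figures reproduce. They are those of a crude test with SD 11 and no gain from baseline.

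**2. Baseline imbalance.** A baseline difference D shifts the crude difference in change by (1 − b) × D in size. With b = 0.5 and D = 3 mmHg the shift is 1.5 mmHg. Under simple randomisation the SE of D is s0 × √(1/42 + 1/21) = 0.267 × s0, that is 2.1 mmHg for s0 = 8 and 2.7 for s0 = 10. Minimisation on the 160 mmHg cut makes it somewhat smaller.

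**3. Precision.** If follow-up has slope b on baseline, change has slope b − 1, so the residual variance after ANCOVA is 121 − (1 − b)² × s0². Power at 5.5 mmHg, 42:21, is from simulation (20,000 trials per row; age, sex and BMI taken as non-prognostic; simple allocation; t on 57 df for both ANCOVA columns):

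| b | s0 | Residual SD | Cut in SD | Crude | ANCOVA | ANCOVA with HC3 |
|---|---|---|---|---|---|---|
| 0.3 | 10 | √72.00 = 8.49 | 23% | 46% | 64% | 59% |
| 0.3 | 8 | √89.64 = 9.47 | 14% | 45% | 54% | 50% |
| 0.5 | 10 | √96.00 = 9.80 | 11% | 46% | 52% | 47% |
| 0.5 | 8 | √105.00 = 10.25 | 7% | 45% | 48% | 44% |
| 0.5 | 7 | √108.75 = 10.43 | 5% | 45% | 47% | 43% |
| 0.7 | 7 | √116.59 = 10.80 | 2% | 45% | 44% | 40% |

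The last row has no gain because covariates are not quite free. Chance imbalance in four covariates multiplies the variance by about 1 + 4/(63 − 4 − 3) = 1.07, so the SE by about 1.035, and 10.80 × 1.035 = 11.2, above 11. Minimisation would soften this cost. Under the null with equal variances (b = 0.5, s0 = 8), rejection rates are 5.1% crude, 4.9% ANCOVA and 4.1% HC3.

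**4. Equal variances at 2:1.** Simulated size at nominal 5%, 42:21, 100,000 trials:

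| Sham SD / active SD | Pooled | Welch |
|---|---|---|
| 0.67 | 2.6% | 5.0% |
| 0.8 | 3.5% | 4.9% |
| 1 | 4.9% | 5.0% |
| 1.25 | 6.9% | 5.1% |
| 1.5 | 8.6% | 5.1% |

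**5. Two unranked tests.** In 20,000 null trials per scenario (b 0.3-0.7, s0 7-10), each test alone held about 5%. Claiming success on either gave 6.4-7.8%, and the two disagreed on significance in 2.8-5.9% of trials.

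**The case against.** ANCOVA is not missing: the article specifies it with the right covariates, and the full SAP, which is not shown, may rank the two analyses. That stands, and it limits the point to which analysis decides. It does not remove the point, because the article itself attaches the null hypothesis to the crude test.

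The gain is uncertain. Eligibility confines daytime SBP to 135 to below 170 mmHg; a uniform spread over that window would have SD 35/√12 = 10.1, so s0 = 10 is near the top of what is plausible. With b = 0.5 and s0 of 7 to 8 the SD falls by only 5-7%. This stands.

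A remedy that relied on HC3 standard errors would defeat itself. In the table HC3 costs about four points of power throughout, which is the whole gain at b = 0.5 with s0 = 8. This stands too, so robust errors belong in a sensitivity analysis.

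Three stronger readings are tempting, and the documents do not support them:
- *The crude test is invalid or biased.* With equal variances it holds its size. Regression to the mean after selection on baseline is expected equally in both arms, so the crude difference is unbiased over randomisation. Only the result conditional on a chance imbalance is affected.
- *The type I error is inflated.* The article gives one SD, 11 mmHg. The unequal ratios above are hypothetical, and inflation needs the sham arm to be the more variable. If response to tAN varies between patients, the larger arm is the more variable one and the pooled test errs on the conservative side.
- *Every secondary endpoint would be adjusted for daytime SBP.* The ordinary meaning of analysing them in the same way is that each is adjusted for its own baseline.

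**Conclusion.** The point holds as a low-cost improvement to a valid plan, and the sample-size figures are correct. The article tests the between-arm hypothesis with the weaker of two analyses it already specifies and does not say which p-value decides.

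For b of 0.3 to 0.5 and s0 of 8 to 10 mmHg, ordinary ANCOVA raises power at 5.5 mmHg with 42:21 from about 45% to 48-64%. For b = 0.7 and s0 = 7 it gains nothing (44% against 45%). Both inputs are assumptions, so the size of the gain is uncertain. Protection against chance baseline imbalance and having one named test are benefits in either case. Replacing pooled by Welch for the crude comparison is a safeguard against a variance difference that the documents neither show nor exclude.

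**What to change.** Before unblinding:

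1. Name one primary between-arm test: ITT ANCOVA of daytime SBP with terms for arm, baseline daytime SBP, age, sex and BMI, using ordinary model-based standard errors. Given baseline as a covariate, change and the Day 84 value yield the same arm effect apart from sign.
2. Show the crude difference in mean change as supportive, with a Welch interval and test in place of the pooled ones.
3. Report heteroscedasticity-robust standard errors for the ANCOVA as a sensitivity analysis only.
4. If the full SAP already ranks the analyses this way, bring the article's sentence into line with it.

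The cost is four degrees of freedom and a wording change; no new data or further model is needed. Timing is the real constraint. The Dissemination section says that recruitment ended in May 2025 and final follow-up was due by September 2025. The change must therefore be dated and shown to precede unblinding. Otherwise it would be a choice of primary test that could have been informed by the results.
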